### 2.6. Data Collection, Management, Statistical Method, and Ethical Considerations

The collection of the data will be performed in paper and later entered electronically. All data will be confidential. Enrolled patients will be registered in anonymous form using an identification code (progressive number), which will be used for data management solely for research purposes. The recorded data will be anonymized to avoid any link with patients. The data will be archived in an Excel program and kept at the trial sites under the responsibility of the principal investigator. Access to the data will be allowed only to personnel directly involved in the research protocol and protected by a password. Patients will not be identified by name in future publications. Participants will be informed about all main aspects of the research and of their right to refuse to take part or to withdraw consent to participation at any moment. An insurance policy to protect the subjects participating in the trial will be stipulated with the insurance company selected by the University of Pisa.

The data will be recorded in a specifically designed database and elaborated by means of the SPSS software (version 26). The Kolmogorov–Smirnov test will be used to examine variables for normal (Gaussian) distribution. Therefore, the comparisons between patients’ groups for variables of non-Gaussian distribution will be performed by means of non-parametric statistical tests; in particular, the Mann–Whitney test for independent samples will be used. The Student’s t-test for independent samples will be used to compare groups for variables of Gaussian distribution. According to non-Gaussian or Gaussian distribution of paired data, the Wilcoxon test and the Friedman test or the Student’s t-test for dependent samples and the repeated measures ANOVA will be used, respectively. The chi-square test will be used to compare the frequencies of categorical variables. Correlations between continuous variables will be examined by means of Spearman’s coefficient in case of non-Gaussian distribution or by means of Pearson’s coefficient in case of Gaussian distribution. A regression analysis will be used to explore the relationship between more variables. A *p* value less than 0.05 will be considered significant.

The study will be conducted in accordance with the 1964 Helsinki Declaration. Ethic codes: Helsinki, Art.3; Helsinki, Article 1; Nuremberg, Art.2; Nuremberg, Art.2; Helsinki, Articles 4, 5, 7; Helsinki, Art.6; Helsinki, Articles 9, 10, 11. The study will be also conducted in accordance to the Directive 2001/20/EC for Clinical Trials. The study protocol has been approved by the Ethics Committee of Area Vasta Nord-Ovest Toscana (Italy).

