## 2. Methods

### 2.1. Study Design, Setting, and Timeline

The study is a controlled, randomized, non-profit parallel group superiority clinical trial fulfilling the CONSORT criteria for non-pharmacological treatment. See Figure 2. The estimated time for the entire duration of the study is 13 months as summarized in the Gantt Chart. See Table 1.

A total of 30 patients will be allocated to either CBT-E or CBT-VR. We opted for 15 patients for each group. Based on a sample of 100 healthcare workers of our University Hospital suffering from Adjustment Disorders and treated with CBT at our center (pre-treatment CGI score = 3.95 ± 0.74 and post-treatment CGI score = 2.39 ± 1.07, unpublished data), to point out a difference between the 2 treatment groups (CBT-E and CBT-VR) of at least 1 point at the CGI, the estimated sample size should be at least 26, with 13 patients in the CBT-E group and 13 patients in the CBT-VR group (by considering confidence interval = 95%, statistical power = 90%, ratio of sample size of 1). 

Participants will be assessed at baseline, during each session of CBT, and at the end of the training. Recruitment will be carried out at the outpatient care setting of INAIL, the Italian National Institute for Insurance against Accidents at Work, a public entity safeguarding workers against physical injuries and occupational diseases. The randomized clinical trial will then be conducted at the Center for Work-Related Stress and Occupational Mental Disorders of a major University Hospital in central Italy (Azienda Ospedaliero-Universitaria Pisana, AOUP). The Center includes a multidisciplinary team comprising occupational physicians, psychiatrists, and psychologists. A Trial Management Team (TMT) will be formed to conduct the day-to-day management of the trial. This will include the chief investigator, trial physicians with different roles, and the data manager. The group will meet at least once per week to discuss issues related to the progress of the trial and to ensure the trial is running well.

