### 2.2. Eligibility Criteria, Tools, and Informed Consent

Recruited subjects will be workers with a diagnosis of AD or PTSD determined by means of the presence of items corresponding to DSM-5 criteria for the disorders. Inclusion and exclusion criteria for randomization in the arms of the study are summarized in Table 2. A case report form will be fulfilled for each participant reporting personal data at the beginning of the training and physiological and clinical data at baseline (T0), at every CBT session, and at the end of the training (T1). Personal background, physiological, and clinical data are summarized in Table 3.

Regarding informed consent, a first information sheet will be handed out at the outpatient clinic of INAIL during the recruitment phase. Subsequently, trial assessors of the Center for Work-Related Stress and Occupational Mental Disorders will discuss the trial, with referred patients considering the information provided in the information sheet. The assessors will then obtain written consent from patients willing to participate in the trial.

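### The arms are compared by a t-test or Mann–Whitney test picked by a normality pre-test, and no stated between-arm comparison adjusts for the T0 values collected

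*Protocol article*

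**What the plan says.** Section 2.6 begins the analysis with a Kolmogorov–Smirnov "test will be used to examine variables for normal (Gaussian) distribution". The outcome of that test decides how the arms are compared. For variables called non-Gaussian, the Mann–Whitney "test for independent samples will be used"; the Student's t-test is the one "for independent samples will be used to compare groups for variables of Gaussian distribution". Neither carries a covariate.

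For paired data the same section lists Wilcoxon and Friedman (non-Gaussian) or the paired t-test and repeated measures ANOVA (Gaussian), with no arm factor named. A regression is mentioned only as exploratory, with no outcome, arm term or baseline covariate.

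Section 2.2 has the case report form record "physiological and clinical data at baseline (T0), at every CBT session, and at the end of the training (T1"). Section 2.5 counts variations of the parameters among the outcomes, without saying whether the arms are compared on T1 values or on changes. Section 2.1 describes a parallel-group superiority trial and states "We opted for 15 patients for each group".

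**The concern.** Two features of the between-arm rule work against a trial of 30 patients.

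First, baseline values are available and the stated comparison does not adjust for them. With 15 per arm and no stratification described in section 2.5, chance differences at T0 can be sizeable. An unadjusted comparison of T1 scores carries them into the estimate, and any T1 variation that T0 could explain stays in the error term.

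Second, the test is not fixed in advance. The t-test and Mann–Whitney address different quantities and do not always agree at the 0.05 level. The choice between them rests on a pre-test whose behaviour depends on the number of patients it is run on and on whether the Lilliefors correction is applied. The article states neither.

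Hypothesis 2 (section 1.2) adds a related gap. It predicts a larger physiological fall under CBT-VR than under CBT-E, which is an arm-by-time contrast. Of the paired methods listed, only repeated measures ANOVA could carry that contrast.

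**Working it through.** **1. The plan's own figure.** Section 2.1 gives a difference "of at least 1 point at the CGI", 95% confidence (taken as two-sided 5%), 90% power, 1:1 allocation, and "pre-treatment CGI score = 3.95 ± 0.74 and post-treatment CGI score = 2.39 ± 1.07". It concludes that "the estimated sample size should be at least 26, with 13 patients in the CBT-E group and 13 patients in the CBT-VR group". The normal approximation is n per arm = 2(1.960 + 1.282)² SD²/δ².

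- SD 0.74: 2 × 10.51 × 0.5476 = 11.5, so 12 per arm. The noncentral-t calculation gives 13, which is the stated 26 in total.
- SD 1.07: 2 × 10.51 × 1.1449 = 24.1, so 25 per arm. Noncentral t gives 26 per arm.

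The stated figure therefore reproduces with the pre-treatment SD. A comparison of end-of-treatment scores would face the post-treatment SD, so 1.07 is used below.

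**2. Power at 15 per arm, 1 point, two-sided 5%.** The T0–T1 correlation r is an assumption, because the article gives none.

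- Unadjusted t-test: SD 1.07, 28 degrees of freedom.
- T0-adjusted: residual SD = 1.07 × √(1 − r²), 27 degrees of freedom.
- Change score: SD = √(1.07² + 0.74² − 2r × 1.07 × 0.74), 28 degrees of freedom.

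| r | Unadjusted | T0-adjusted (SD) | Change score (SD) |
|---|---|---|---|
| 0 | 69.5% | 69.4% (1.070) | 52.9% (1.301) |
| 0.3 | 69.5% | 73.5% (1.021) | 66.9% (1.103) |
| 0.5 | 69.5% | 81.3% (0.927) | 79.5% (0.949) |
| 0.7 | 69.5% | 93.2% (0.764) | 93.3% (0.764) |

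Direct simulation of the adjusted model gave slightly lower power, because the formula ignores the cost of chance T0 imbalance: 68.4%, 79.4% and 92.5% at r = 0, 0.5 and 0.7, against about 69–70% unadjusted. With the smaller SD of 0.74, power is 94.6% unadjusted and 98.4% adjusted at r = 0.5, so the gain is modest there.

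**3. The gate.** Share of simulated samples called non-normal at 5% (20,000 per shape, no arm effect):

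| Shape | n = 15, Lilliefors | n = 15, uncorrected | n = 30 pooled, Lilliefors | n = 30 pooled, uncorrected |
|---|---|---|---|---|
| Normal | 5% | 0% | 5% | 0% |
| Lognormal (σ 0.5) | 26% | 0.7% | 48% | 4% |
| Gamma (shape 2) | 24% | 0.4% | 46% | 2% |
| t, 3 df | 21% | 2% | 34% | 6% |
| Exponential | 45% | 2% | 79% | 12% |
| Rounded 7-point score (mean 2.39, SD 1.07) | 69% | 4% | 99.9% | 32% |

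At a 1-SD effect the t-test and Mann–Whitney gave different 0.05 verdicts in 6% of trials for normal data and in 10–14% for the four continuous non-normal shapes. With no effect, the two-stage rule (Lilliefors version, run in each arm) rejected in 5.0–5.4% of trials for the five continuous shapes and 4.4% for the rounded score.

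**4. Hypothesis 2 against the listed methods.** Wilcoxon, Friedman and the paired t-test contain no arm term. Repeated measures ANOVA can contain one, but none is stated. Under the gate it gives way to Friedman whenever the data are called non-Gaussian.

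**The case against.** The other side has several good points.

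- A reader might infer that T0 is ignored altogether. The article does not support that. The paired tests use T0, and the variations in section 2.5 may mean change scores compared between arms. On that reading most of the power difference disappears at correlations of 0.5 and above. What remains is that the article does not say so, and that change scores do worse than adjustment at low correlation (52.9% against 69.4% at zero).
- A reader might infer that Hypothesis 2 cannot be tested with the listed methods. That goes too far: repeated measures ANOVA is listed and could include arm by time. The model terms may be set out in a fuller document. The switch to Friedman is, however, a rule written here, and it removes the arm term.
- The gate need not be run on 15 patients. Pooling all 30 is not excluded, and the corrected test then detects exponential data in 79% of samples.
- For a coarse 7-point score the choice is not a coin toss. With the correction, at least one arm is rejected in 90% of trials; without it, 4% of arms are. There the software option decides more than chance does, and Mann–Whitney is a reasonable test for such a score.
- CGI-I is rated relative to baseline and has no T0 value, so the power figures cannot be read as a gain for CGI-I.
- An unadjusted comparison in a randomised trial is valid.

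All of this narrows the point. None of it supplies a stated between-arm comparison that adjusts for T0, or a test chosen in advance.

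**Conclusion.** The point holds as one of precision and pre-specification. Section 2.6 fixes a data-driven choice between two covariate-free tests, while T0 values are available and no stated between-arm comparison adjusts for them.

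It would be wrong to conclude that false-positive rates are inflated: in simulation the two-stage rule stays close to 5%.

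For a score measured at T0 and T1 with SD 1.07 and a 1-point difference, leaving out T0 costs about 4, 12 and 24 percentage points of power at correlations of 0.3, 0.5 and 0.7, and nothing near zero. If change scores are what is meant, adjustment gains about 7 points at 0.3, 2 at 0.5 and none at 0.7. These sizes rest on an assumed correlation and on CGI standard deviations borrowed as an illustration. The article gives no SD for the scales to which the adjustment would apply.

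**What to change.** - Delete the Kolmogorov–Smirnov gate for between-arm comparisons.
- For each scale scored at both T0 and T1 (such as BDI-II, SAS, PSQI and DTS), pre-set one linear model of the T1 score on arm and T0 score, reported as an adjusted mean difference with 95% confidence interval.
- For the session-by-session physiological measures, use a linear mixed model with arm, session and their interaction, and take the arm-by-session term as the test of Hypothesis 2's larger fall.
- Compare CGI-I between arms with one test named in advance, without a baseline of its own.
- Give a rank-based or permutation version of each comparison as a sensitivity analysis.
- Adjustment for diagnosis (AD or PTSD) is optional, since the article names no stratification factor.

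The cost is a rewording of section 2.6 and one degree of freedom per covariate. No new data are needed, because T0 is already recorded. If T0 turns out to be uncorrelated with T1, the loss is small: 69.5% to 69.4% by formula, 70.0% to 68.4% in simulation.

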### 2.3. Measures

The whole sample will be investigated by means of the BDI-II, SAS, JCQ, PSQI, PDI, DTS, and CGI-I.

The BDI-II consists of 21 groups of statements and is one of the most widely used psychometric tests for measuring the severity of depression. This questionnaire presents statements that describes the way the patient has been feeling (quotes about sadness, pessimisms, loss of pleasure, guilty feelings [..]) during the past two weeks. Answers are scored on a scale value of 0 to 3. A total score of 0–13 is considered minimal range, 14–19 is mild, 20–28 is moderate, and 29–63 is severe, e.g., 0, I do not feel sad; 1, I feel sad much of the time; 2, I am sad all the time; 3, I am so sad or unhappy that I can’t stand it. The Italian version of the BDI-II was administered to a sample of 723 college students and to a sample of 72 depressed patients. Alpha and test-retest reliabilities were computed along with associations with age and education. The BDI-II proved a reliable and valid measure of depressive symptoms in the Italian context [19].

The SAS is a 20-item self-report assessment device built to measure anxiety levels based on scoring in 4 groups of manifestations: cognitive, autonomic, motor, and central nervous system symptoms. Answering the statements, a person should indicate how much each statement applies to him or her within a period of one or two weeks prior to taking the test. Each question (“I feel tense, nervous, restless, or agitated”) is scored on a Likert-type scale of 1–4 (based on these replies: “a little of the time,” “some of the time,” “good part of the time,” “most of the time”). Some questions are negatively worded to avoid the problem of set response. The overall assessment is based on the total score. The total raw scores range from 20 to 80. The raw score then needs to be converted to an “Anxiety Index” score using the chart on the paper version of the test. The “Anxiety Index” score can then be used to determine the clinical interpretation of one’s level of anxiety: 20–44, Normal Range; 45–59, Mild to Moderate Anxiety Levels; 60–74, Marked to Severe Anxiety Levels; 75 and above, Extreme Anxiety Levels (e.g., 0, I do not feel sad; 1, I feel sad; 2, I am sad all the time and I can’t snap out of it; 3, I am so sad and unhappy that I can’t stand it). This tool has been translated and validated in many languages, including Italian. The internal consistency reliability coefficient was 80 [36].

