The PDI is a self-report instrument developed to retrospectively measure the distress experienced by the subject at the time of the potentially traumatizing event or immediately after. It is composed of 13 items, each scored on a 5-point Likert-type scale ranging from 0 to 4 (0 = not at all, 1 = slightly, 2 = somewhat, 3 = very, and 4 = extremely true), with the total score ranging from 0 to 52, and higher scores indicating increased distress. Statements explore cognitive response to the trauma (e.g., I thought I might die), emotional distress (e.g., I was horrified by what happened) or physical symptoms (e.g., I had physical reactions like sweating, shaking, and pounding heart). The PDI demonstrates good test–retest reliability, convergent and divergent validity, and good internal consistency. The internal consistency of the PDI was satisfactory with a Cronbach’s alpha of 0.87. The reliability, validity, internal consistency, and the temporal stability of the Italian version of the PDI resulted to be good, falling within the range of those reported in the original validation study [39].

The DTS is a self-report instrument developed to assess DSM PTSD symptoms. It is a 5-point Likert-type scale, self-report instrument that assesses the DSM symptoms of PTSD. It is composed of 17 items, each scored on a 5-point Likert-type scale evaluating frequency (0 = “not at all” to 4 = “every day”) and severity (0 = “not at all distressing” to 4 = “extremely distressing”) of the most disturbing trauma (e.g., of statements: Have you had painful images, memories, or thoughts of the event?). Respondents rate how much trouble they have had with each symptom. The scale demonstrated good test–retest reliability (r = 0·86), internal consistency (r = 0·99). The Italian version of the tool by Pieraccini et al. (1999) has been approved by the original authors [13,40].

The clinical global impression-improvement scale (CGI-I) is a 7-point scale that requires the clinician to assess how much the patient’s illness has improved or worsened relative to a baseline state at the beginning of the intervention. (e.g., clinicians ask: “Compared to the patient’s condition at baseline, this patient’s [average] condition has...?” and rate as: Very much improved; Much improved; Minimally improved; No change; Minimally worse; Much worse; Very much worse). The Italian version of the tool has been approved by the National Institute of Mental Health [41].

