### 2.5. Procedures, Outcomes, and Adverse Events

Participants will be randomized with a 1:1 ratio for CBT-E or CBT-VR without any specific criteria in order to prevent any randomization bias. Researchers involved in the outcome measures will be blinded to the allocation. Both the CBT training are assumed to be appropriate and beneficial for participants based on evidence from the literature. The training for each individual subject will begin within 7 days from T0, and each patient will perform 8 sessions of CBT-E/CBT-VR distributed 1 every week. If the subject is unable to perform the session on the scheduled day, a new date will be agreed within one week, failing which the patient would be excluded from the study. The intervention will also be discontinued if the participant withdraws consent or if a change in circumstance results in the participant meeting the trial exclusion criteria and becomes unsafe to engage in the intervention, or if any side effects would arise. These participants will remain in the analysis for data collected up until the date of withdrawal. The intervention is individualized, and progression/modification will be determined through discussions with the subject and the other members of the trial team. Every discontinuation will be replaced in order to reach the trial sample size.

The training protocol of CBT-E/CBT-VR is summarized in Table 5.

All outcomes will be performed before, during, and after the intervention phase, which is 10 weeks in total. The first week involves enrollment, randomization, and baseline data; the second to ninth week involves the training program; and the tenth week involves the patient final report. The outcomes measured will be physiological and clinical parameters, as well as their variations/comparison during the two training programs.

In particular, the physiological signs of stress reporting variations of temperature, skin conductance, heart rate, and respiratory rate will be recorded.

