## 3. Discussion

Globally, in the literature, the application of VR has been considered in many fields, but researchers in Italy have not yet explored the possibility of using it for the widespread exposure of CBT therapy in the work context with the aim of being able to define standardizable and short rehabilitation paths for the improvement of the mental health of workers.

The outcomes of this trial will determine whether CBT rehabilitation can improve the mental health of workers suffering from occupational stress diseases. The secondary outcomes will determine the superiority of VR rehabilitation program with respect to normal exposure therapy.

In summary, the novelty of this study protocol is that, for the first time, a trial explored the efficacy of CBT rehabilitation for Italian workers affected by occupational stress diseases and attempted to determine whether CBT through virtual reality is an advantage to a classical exposure therapy. The work-related stress diseases rehabilitation program described in this protocol has been designed to be amenable to be reproduced and offered to workers. The future application is to offer workers a treatment option with evidence of effectiveness and allow a more rapid reintegration into work.

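### No outcome or time point is named as primary for the VR versus CBT-E comparison, so the 5% error rate does not cover a claim of VR superiority

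*Protocol article*

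**What the plan says.** Section 2.1 describes a "controlled, randomized, non-profit parallel group superiority clinical trial". It derives the sample size from a one-point CGI difference between the two arms; no other measure is used for sizing.

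Section 2.3 lists seven scales: "The whole sample will be investigated by means of the BDI-II, SAS, JCQ, PSQI, PDI, DTS, and CGI-I". Section 2.5 adds four signals ("variations of temperature, skin conductance, heart rate, and respiratory rate will be recorded") and defines the outcomes collectively: "The outcomes measured will be physiological and clinical parameters, as well as their variations/comparison during the two training programs". On timing it says: "All outcomes will be performed before, during, and after the intervention phase". Nothing is ranked.

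Section 2.6 lists two-sample and paired tests, repeated-measures methods, chi-square, correlations and regression. It closes with one criterion for all of them: a p "value less than 0.05 will be considered significant".

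The Discussion (section 3) then states: "The secondary outcomes will determine the superiority of VR rehabilitation program with respect to normal exposure therapy". The article does not say which outcomes are secondary, and it defines no primary.

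**The concern.** Whether VR exposure beats imaginal exposure is the randomized question and the one the trial is sized for. The article does not say which result answers it. Section 2.1 points to CGI, section 2.5 to every measure equally, and the Discussion to a set of secondary outcomes that is never listed.

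CGI cannot simply be assumed to be primary. Section 2.1 uses a CGI score taken before and after treatment (3.95 and 2.39). The only CGI instrument listed in section 2.3 and Table 3 is CGI-I, which rates change from baseline and is a different quantity.

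The choice of deciding outcome is therefore still open when the results are seen. With about ten candidates, each tested at 0.05, the nominal error rate does not apply to the overall VR conclusion.

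**Working it through.** **1. The plan's own figure.** Inputs from section 2.1: difference 1 CGI point, SD 0.74 before and 1.07 after treatment, 95% confidence, 90% power, ratio 1. The SD used and the sidedness are not stated; two-sided is assumed. Per arm, n = 2(1.960 + 1.282)² × SD² / 1².
- SD 0.74: 2 × 10.51 × 0.5476 = 11.5, so 12. The exact noncentral-t calculation gives 13, which is the stated 26 in total.
- SD 1.07: 2 × 10.51 × 1.1449 = 24.1, so 25 (26 by noncentral t).
- A change score with an assumed pre–post correlation of 0.7 has SD 0.764 and also gives 13 by the normal formula.

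The stated 26 thus fits one two-sided test of one outcome at 0.05, with no allowance for multiplicity. Which SD is right is a separate question.

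**2. Count of outcomes.** 7 scales + 4 signals = 11. PDI is described as "developed to retrospectively measure the distress experienced by the subject at the time of the potentially traumatizing event or immediately after" and JCQ describes the job. If both are only descriptors, 9 remain.

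**3. Error under identical arms, one between-arm test per outcome, independent outcomes.**
- Any false difference: 1 − 0.95^11 = 0.431; 1 − 0.95^9 = 0.370.
- At least one favouring VR (0.025 per test in that direction): 1 − 0.975^11 = 0.243; 1 − 0.975^9 = 0.204.
- One named primary, favouring VR: 0.025.

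**4. Correlated outcomes.** The documents give no correlations, so a range is assumed. Simulation of 40,000 null trials, 15 per arm, 11 equally correlated normal outcomes, two-sample t-tests:

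| Assumed correlation | Any false difference | At least one favouring VR |
|---|---|---|
| 0 | 43.1% | 24.2% |
| 0.3 | 37.8% | 19.2% |
| 0.5 | 31.1% | 15.8% |
| 0.7 | 23.0% | 11.5% |

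**5. Adjusting across all outcomes instead.** Bonferroni over 11 sets each test at 0.05/11 = 0.00455; familywise error is then 1 − (1 − 0.00455)^11 = 4.9%. With 15 per arm, power for one CGI point falls from about 95% to 72% (SD 0.74), or from about 70% to 32% (SD 1.07). A single primary outcome suits this sample size better.

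**The case against.** **This is a condensed article, and multiplicity belongs in an SAP.** That holds for the adjustment method: the absence of a named procedure is not the point. Naming the outcome that decides a superiority trial is a protocol-level choice. Here the article also speaks to it and conflicts with itself, because the trial is sized on a between-arm difference while superiority is assigned to secondary outcomes with no primary defined.

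**CGI is primary by implication, because it is the powered measure.** This has weight and makes CGI the natural choice. But the article never says so, and the CGI score in section 2.1 is not the CGI-I listed for collection.

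**The Discussion implies an order: benefit of CBT overall first, VR second.** It does, but it still names no outcome for either question.

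**Stronger readings that the documents do not support:**
- A reader might infer that a false VR claim is likely. The 43% counts errors in both directions; the VR-favouring figure for 11 outcomes is at most about 24%. Passing 50% would take 28 independent tests.
- A reader might infer that any single significant result would count as superiority. Section 2.6 sets a threshold for tests, not a rule for the trial's conclusion. The defect is that there is no such rule.
- A reader might add the four signals at each of eight sessions (32 + 7 = 39 tests; 63% favouring VR if independent, about 30% at correlation 0.5). No session-by-session testing between arms is specified: section 2.6 names repeated-measures ANOVA and the Friedman test, and Hypothesis 2 refers only to the first and last sessions.
- Counting PDI and JCQ as outcomes is one reading. Table 3 lists them beside demographic and work data, while section 2.5 does not exclude them. Hence both 11 and 9 are shown.

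**Conclusion.** The point holds in this form: no primary outcome or time point is fixed for the VR comparison, every test uses the same unadjusted threshold, and the Discussion rests superiority on unnamed secondary outcomes.

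For identical arms, the chance of at least one result favouring VR is about 12–24% with 11 outcomes, against 2.5% for one named primary: roughly five to ten times as high. In either direction it is about 23–43%. With 9 independent outcomes the figures are 20% and 37%.

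These figures assume two-sided tests, one between-arm test per outcome at one time point, and a common correlation between 0 and 0.7. They measure how much room the plan leaves; they do not predict that a false claim will be made. The change should be made, because it decides whether the main result can be interpreted.

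**What to change.** - In sections 2.5 and 2.6, name the between-arm CGI comparison at T1 as the single primary outcome, tested at two-sided 0.05.
- State which CGI is meant. If it is the CGI score of section 2.1, add it to section 2.3 and Table 3 at T0 and T1. If it is the listed CGI-I, re-base the sample size on that scale.
- Label the other symptom scales (BDI-II, SAS, PSQI, DTS) and the first- and last-session physiological contrasts of Hypothesis 2 as secondary. Either adjust them for multiplicity or report them as supportive, without a superiority claim. Which of the two is the sponsor's choice, and the method can sit in the SAP.
- Use PDI and JCQ as baseline descriptors.
- Reword the Discussion so that VR superiority rests on the primary outcome.

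**Cost.** Fewer results can support a superiority claim. If the section 2.1 score is chosen, one brief additional CGI rating is needed at T0 and T1; if CGI-I is chosen, the sample size must be recalculated and may change. The rest is wording.
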